**Table 2. Number of events, accumulated person-time, and HRs for cancer associated with eczema, Denmark**

|                          | N | events | P-Y
at
risk | Rate
per
1,000 | Hazard ratio and 99%
confidence interval  |                    |
|--------------------------|---|--------|-------------------|----------------------|----------------------------------------------------------|--------------------|
|                          |   |        |                   |                      | Unadjusted                                               | Mediation
model |
| Any cancer               |   |        |                   |                      |                                                          |                    |
| Unexposed                |   |        |                   |                      |                                                          |                    |
| Exposed                  |   |        |                   |                      |                                                          |                    |
| Lung cancer              |   |        |                   |                      |                                                          |                    |
| Unexposed                |   |        |                   |                      |                                                          |                    |
| Exposed                  |   |        |                   |                      |                                                          |                    |
| Breast cancer            |   |        |                   |                      |                                                          |                    |
| Unexposed                |   |        |                   |                      |                                                          |                    |
| Exposed                  |   |        |                   |                      |                                                          |                    |
| Prostate cancer          |   |        |                   |                      |                                                          |                    |
| Unexposed                |   |        |                   |                      |                                                          |                    |
| Exposed                  |   |        |                   |                      |                                                          |                    |
| Melanoma skin cancer     |   |        |                   |                      |                                                          |                    |
| Unexposed                |   |        |                   |                      |                                                          |                    |
| Exposed                  |   |        |                   |                      |                                                          |                    |
| Keratinocyte skin cancer |   |        |                   |                      |                                                          |                    |
| Unexposed                |   |        |                   |                      |                                                          |                    |
| Exposed                  |   |        |                   |                      |                                                          |                    |
| Lymphoma                 |   |        |                   |                      |                                                          |                    |
| Unexposed                |   |        |                   |                      |                                                          |                    |
| Exposed                  |   |        |                   |                      |                                                          |                    |
| Multiple myeloma         |   |        |                   |                      |                                                          |                    |
| Unexposed                |   |        |                   |                      |                                                          |                    |

## Analysis plan

---

|                                                                                     |
|-------------------------------------------------------------------------------------|
| Exposed                                                                             |
| Leukaemia                                                                           |
| Unexposed                                                                           |
| Exposed                                                                             |
| Meningioma                                                                          |
| Unexposed                                                                           |
| Exposed                                                                             |
| Cancer of the brain, hypophysis,
corpus pineale and ductus
craniopharyngealis |
| Unexposed                                                                           |
| Exposed                                                                             |
| Spinal cord, cranial nerve and
other CNS tumours                                 |
| Unexposed                                                                           |
| Exposed                                                                             |

---

Estimated hazard ratios from Cox regression with time since index date as underlying timescale, stratified by matched set.

Unadjusted: No adjustment.

Mediation model: Adjusted additionally for time-varying lifestyle-related diseases.

4. For the atopic eczema cohort, we will make a plot of the cumulative incidence function by age for overall and specific cancers (lung, breast, prostate, lymphoma, leukemia, multiple myeloma, CNS cancers, melanoma and keratinocyte cancer) non-parametrically. This will be done for the unadjusted model.
5. We will assess the assumption of proportional hazards model in all the primary analysis models through Schöenfeld residual plots.

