## Analysis plan

### *Eczema exposed*

- Persons with a diagnosis of atopic eczema (ICD-8: 691; ICD-10: DL20) in the Danish National Patient Registry between 1 Jan 1977 and 10 February 2018.
- We include all primary and secondary diagnoses for eczema from admissions, hospital outpatient clinics and emergency rooms in the Danish National Patient Registry, including ongoing contacts (that is, persons who at the end of study period are in active follow-up in a hospital outpatient clinic).
- Index date = The earliest hospital record for atopic eczema (date of admission or first outpatient appointment).
- Only persons who are born in Denmark and living in Denmark on the index date (i.e. date of first record for eczema).

For the current study, we will further restrict the study population as follows:

- We will exclude eczema patients (together with their matched comparators) identified by an ICD-8 diagnosis recorded together with an additional (“modification”) code indicating that it potentially an uncertain/unverified/working diagnosis (c\_diagmod=1–7).
- We will exclude patients (together with their matched comparators) with inconsistencies in registration of status and residence in the Civil Registration System (recorded as alive but not living in Denmark but without an emigration date), as we assume that these patients are not living in Denmark and thus not eligible.
- To ensure that we have at least 1 year of registration history from included registries (except the prescription registry), we will only include patients (together with their matched comparators) with index date on 1 January 1982 or later. In the subanalysis on severity and in a sensitivity analysis, we restrict to those diagnosed on 1 January 1996 or later in order to ensure one year of registration history in all databases.
- To ensure at least 1 year of follow-up after start of eligible follow-up (available until 30 June 2017), we will include eczema patients until 30 June 2016.
- We will exclude eczema patients (together with their matched comparators) with a record for any cancer (except non-melanoma skin cancer) before or on index date (see Table 2). That is, we will not only exclude those with history of the cancer outcome of interest. However, in analyses of non-melanoma skin cancer specifically, we will exclude those with previous history of this cancer as well.

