### Follow-up

- Follow-up start: index date.
- Follow-up end: earliest of emigration, death, end of study (30 June 2017) or first-ever cancer diagnosis (when examining specific cancers, patients are thus censored if diagnosed with another individual cancer).
- If a person from the comparison cohort is diagnosed with eczema during follow-up, that person will be censored at time of diagnosis. The person will then contribute to the eczema cohort together with his/her own comparators (this has been accounted for in the sampling done by the Danish Health Data Authority)

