## Analysis plan

3. With time since index date as underlying time scale, we will use stratified Cox regression (conditioning on matched set) to compute unadjusted hazard ratios (99% confidence intervals) to determine associations between eczema and each outcome (that is, comparing eczema patients and the comparison cohort). By stratifying on matched set, the model accounts for birth year, sex and calendar period. We will then fit a “mediation model” additionally adjusting for time-varying lifestyle-related diseases (chronic obstructive pulmonary disease, hyperlipidemia, hypertension, alcohol-related conditions, ischemic heart disease, hospital-diagnosed obesity and type II diabetes). If sufficient power, we will adjust for the lifestyle-related diseases as individual variables.

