## Analysis plan

Cancer of the brain, hypophysis,  
corpus pineale and ductus  
craniopharyngealis

Unexposed

Exposed

Spinal cord, cranial nerve and  
other CNS tumours

Unexposed

Exposed

Estimated hazard ratios from Cox regression with time since index date as underlying timescale, stratified by matched set. Adjusted additionally for **systemic treatment for eczema**.

Unadjusted: No adjustment.

Mediation model: Adjusted additionally for time-varying lifestyle-related diseases and **systemic treatment for eczema**.

9. We will repeat the main analysis after starting follow-up at 3 years after index date to limit potential reverse causality. If we see a large change at 3 years, we will also repeat the main analysis by changing start of follow-up to 5 years after index date.

**Table 9. Number of events, accumulated person-time, and HRs for cancer associated with eczema, Denmark. Starting follow-up at 3 years after index date.**

|                          | N | events | P-Y
at
risk | Rate
per
1,000 | Hazard ratio and 99%
confidence interval  |                    |
|--------------------------|---|--------|-------------------|----------------------|----------------------------------------------------------|--------------------|
|                          |   |        |                   |                      | Unadjusted                                               | Mediation
model |
| Any cancer               |   |        |                   |                      |                                                          |                    |
| Unexposed                |   |        |                   |                      |                                                          |                    |
| Exposed                  |   |        |                   |                      |                                                          |                    |
| Lung cancer              |   |        |                   |                      |                                                          |                    |
| Unexposed                |   |        |                   |                      |                                                          |                    |
| Exposed                  |   |        |                   |                      |                                                          |                    |

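### Proportional hazards is checked only by residual plots and no table gives the eczema HR by time since index, so a late association, or an early and a late one together, cannot be read from the planned tables

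*Protocol*

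**What the plan says.** The main model is set in Statistical analyses, item 3: "With time since index date as underlying time scale, we will use stratified Cox regression", conditioning on matched set, with 99% confidence intervals. Eczema patients enter "with index date on 1 January 1982 or later", and "we will include eczema patients until 30 June 2016". The Follow-up section has "Follow-up start: index date", with the end at the "earliest of emigration, death, end of study (30 June 2017) or first-ever cancer diagnosis".

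Item 5 is the only provision on proportional hazards: "We will assess the assumption of proportional hazards model in all the primary analysis models", using Schoenfeld residual plots. It gives no criterion and no consequence. Each HR table shell holds one HR per model and contrast, and none has rows by time since index. Item 4 plots cumulative incidence, but only in the eczema cohort and by age, so it does not show how the contrast with comparators changes over follow-up.

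The nearest thing to a time-specific analysis is Sensitivity analyses, item 9: "We will repeat the main analysis after starting follow-up at 3 years after index date to limit potential reverse causality". A 5-year start is added only if the 3-year result differs substantially, and no threshold is given for that.

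**The concern.** When the HR changes over follow-up, a single Cox HR is a weighted average, and the weights depend on when events and censoring happen to fall. For cancer after a first hospital eczema diagnosis, timing carries much of the interpretation. An excess confined to the first years suggests detection or reverse causality, while one that appears after a decade is closer to what the primary aim asks about. The plan recognises the first possibility in item 9 but produces nothing that would show the second, or the two combined. The plots may hint at a trend, but the plan commits to no estimate or interval by period, and any cut-points would then be chosen after the plots have been seen.

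**Working it through.** The protocol states no sample size, event count or maximum follow-up, so there is no figure of its own to reproduce.

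**Step 1: length of follow-up, from the stated dates.**
- Main analysis, 1 January 1982 to 30 June 2017: 35.49 years.
- Severity table and Table 13 (index from 1 January 1996): 21.5 years.
- Activity table (index from 1996, start at month 12): 20.5 years.
- Table 9: years 3 to 35.5, a span of 32.5 years. With the 5-year start the span is 30.5 years.
- A patient entering on 30 June 2016 has at most 1.0 year.

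**Step 2: what a single HR averages.** Take full sets of one patient and 10 comparators (the protocol allows up to 10). Let w_j be the share of comparator events in period j and h_j the true HR there. The score equation for one constant HR θ is

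Σ w_j [h_j − (h_j + 10) θ/(θ + 10)] = 0, which gives θ = Σ w_j h_j.

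**Step 3: illustrations with assumed event shares.**
- *Purely early effect:* HR 2.0 in year 1 with 5–10% of events, 1.0 afterwards. Table 2: 0.05 × 2.0 + 0.95 × 1.0 = 1.05, up to 0.10 × 2.0 + 0.90 × 1.0 = 1.10. Table 9: 1.00. The comparison exposes it.
- *Late effect:* HR 1.0 to year 10, 1.5 afterwards, with 30–50% of events after year 10. Table 2: 0.7 + 0.3 × 1.5 = 1.15, up to 0.5 + 0.5 × 1.5 = 1.25. If 20% of events fall before year 3, the late share from year 3 is 0.30/0.80 = 0.375 up to 0.50/0.80 = 0.625. Table 9 is then 1 + 0.5 × 0.375 = 1.19, up to 1 + 0.5 × 0.625 = 1.31. Neither table shows the null first decade or the 1.5.

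**Step 4: the same with shares derived from the accrual window.** Assume uniform entry from 1982.0 to 2016.5, administrative censoring only, and a baseline hazard rising 0%, 3% or 6% per year since index. The share of comparator events after year 10 is then 0.52, 0.62 or 0.72, and before year 3 it is 0.16, 0.11 or 0.08.

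| True pattern | Table 2 | 3-year start | 5-year start |
|---|---|---|---|
| 1.5 in years 0–3, then 1.0 | 1.04–1.08 | 1.00 | 1.00 |
| 1.0 to year 10, then 1.3 | 1.16–1.22 | 1.19–1.23 | 1.21–1.25 |
| 1.5 in years 0–3, 1.0 in years 3–10, then 1.3 | 1.24–1.25 | 1.19–1.23 | 1.21–1.25 |

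The second row looks much like a constant HR near 1.2. In the third row the shift at 3 years is 0.02 to 0.05, which hides both features and may not prompt the 5-year run.

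**Step 5: what precision to expect.** With events split equally into an early and a late half, e exposed and u unexposed in each, the 99% factor for the late/early HR ratio is exp(2.576 × √(2(1/e + 1/u))).
- e = 15, u = 150 (330 events in all): 2.68.
- e = 150, u = 1,500 (3,300 events in all): 1.37.

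Band-specific HRs would therefore be informative for common outcomes and weak for rare ones.

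**The case against.** The best defence is that the plan already covers the early part of follow-up. Item 9 removes the first 3 years, item 16 takes skin cancers out of the all-cancer outcome, and item 17 looks at melanoma by stage. That stands: a reader might infer that an early detection excess would go unnoticed, but in Step 3 it falls from 1.05–1.10 to 1.00 between Tables 2 and 9. A late excess moves the other way and stays above 1, so in these late-effect scenarios the primary question is answered in the right direction, only diluted.

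Three further limits also stand. First, 35.5 years applies to the main analysis and its unrestricted repeats, not to every table (Step 1). Second, a reader might conclude that the Table 2 HR describes no period of follow-up. That holds only if hazards are in fact non-proportional, and the protocol has no data on this. Third, the residual plots should not be dismissed as uninformative: the text does not exclude scaled, smoothed residuals, and the difficulty with rare cancers is a shortage of events that would limit any method, including time bands.

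It can also be said that a fallback for failed proportional hazards belongs in a separate statistical analysis plan, which may exist. This lowers the weight of the point but does not remove it. The document is itself headed as an analysis plan, chooses the diagnostic and sets out the table shells.

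**Conclusion.** The point holds as a cheap improvement to the plan. It does not show that the primary analysis is invalid. The Table 2 HR is one average over up to 35.5 years, and no table shows how the eczema HR varies with time since index. Item 9 deals with a purely early excess. It does not show the size or timing of a late association, or separate an early from a late one. In the illustrations a late HR of 1.5 reads as 1.15–1.25 in Table 2 and 1.19–1.31 in Table 9, and a late HR of 1.3 as 1.16–1.22 and 1.19–1.23. These figures rest on assumed HR patterns, assumed event shares or accrual, and full 1:10 sets. They show what the planned tables could hide, not what the data will show.

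**What to change.** In item 5, add a supplementary table for the outcomes in results Table 2. It should give the eczema HR with 99% CI in prespecified bands of time since index, for example 0–<3, 3–<10 and 10 years or more, so that the first cut matches item 9. Estimate these from the same matched-set Cox model with an exposure-by-period interaction. Merge adjacent bands with fewer than 20 events, in line with the plan's own threshold for publishing an outcome, and state whether the count covers both cohorts. Describe the Table 2 HR as an average over follow-up, to be read together with the band-specific HRs.

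The cost is one interaction term and one table, with no new data. The downside is wide intervals for rare cancers. A band with 20 events in both cohorts combined would, at HR 1 and 1:10, hold about 20/11 = 1.8 exposed events, and its 99% factor would be exp(2.576 × √(1/1.82 + 1/18.2)) ≈ 7.4. Such bands should be reported as imprecise and not read as evidence of a constant HR.

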**Subgroup analyses**

Depending on power, subgroup analyses may only be performed for overall cancer.

6. We will explore whether the association between eczema and cancer differs by eczema severity or eczema disease activity by stratifying separately on disease severity (Table 4) and activity (Table 5). The severity and activity analyses will be restricted to those with index date on or after 1 January 1996 to ensure at least 1 year of prescription history. Furthermore, the follow-up will start at 12 months after index date in the activity analysis in order to allow categorization of activity.

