### **Objectives, Specific Aims and Rationale**

- Primary aim: To examine if atopic eczema is associated with increased risk of all cancers and a number of specific cancers.
- Secondary aim: To examine if the risk depends on severity and activity of eczema, age, sex, coexisting asthma and systemic immunosuppressive treatments.

Of note, the study will also be conducted by colleagues in the United Kingdom in parallel.

**Study Design:** Nationwide matched cohort study.

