### *Exposure subgroups*

For the secondary aim, we will identify severe and active eczema. The analyses will be performed if feasible in terms of sample size.

We will categorize severity as moderate or severe. Severe eczema will be defined as (1) either phototherapy or systemic treatment for eczema (cyclosporine, azathioprine, mycophenolate, methotrexate, dupilumab), identified in Patient Registry (procedure codes: “BNGA1” “BNGA2” “BNGA3” “BNGA4” “BOHJ18B8” “BWHB83” “BWHA115” “BOHJ20” “BOHJ22”) or Prescription Registry (ATC codes: “L04AX01” “L01BA01” “L04AX03” “L04AD01” “L04AA06” “D11AH05”) or (2) admission to hospital with eczema as the primary reason for admission (i.e. where eczema is recorded in the primary diagnostic position for an in-hospital contact). Severity will be included as a time-updated variable. Thus, a patient with eczema will be classified as having moderate eczema from index date (unless they develop severe eczema). When (and if) a person fulfills the definition for severe eczema, we will classify them as having severe eczema from the

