## Analysis plan

point at which they meet the definition for ‘severe eczema’. Once a person fulfills the criteria for severe disease, he/she will remain in that category for the rest of follow-up. At any given point during follow-up, atopic eczema patients will therefore belong to one of two severity categories: moderate or severe.

We will classify activity of eczema based on consultation and treatment patterns within the first year after index date, as illustrated in the Figure below. A person will be considered to have active eczema that lasts 3 months from either 1) a consultation to a private-practicing dermatologist (any consultations coded with specialty ‘04’ in The Danish National Health Service Registry), 2) a primary care prescription for eczema therapies (Prescription Registry ATC codes: “D07” “D11AH01” “D11AH02” “L04AX01” “L04AX03” “L04AD01” “L04AA06” “H02AB” [excluding injections] or Patient Registry procedure codes: “BNGA1” “BNGA2” “BNGA3” “BNGA4” “BOHJ18B8” “BWHB83” “BWAH115” “BOHJ20” “BOHJ22”) or 3) a hospital record for eczema. Each time a person fulfills one of these criteria, the active period will be extended by 3 months from that date. We will then compute the percentage of time with active eczema in the first 12 months after index date as the number of months with active eczema divided by 12 months. We will then classify persons as: 0=unexposed; 1=those who never had active atopic eczema in the first year; 2=those who had active atopic eczema for less than 50% of the first year; 3=those who had active atopic eczema for at least 50% of the first year. In order to classify activity, follow-up will start at 12 months after index date in activity analyses. Note that periods of disease activity will be identified irrespective of the classification for disease severity.

**Figure.** Illustration of active eczema disease

[figure not shown]

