**Table 3. Number of events, accumulated person-time, and HRs for cancer associated with eczema severity, Denmark**

|                    | N | events | P-Y
at
risk | Rate
per
1,000 | Hazard ratio and 99%
confidence interval  |                    |
|--------------------|---|--------|-------------------|----------------------|----------------------------------------------------------|--------------------|
|                    |   |        |                   |                      | Unadjusted                                               | Mediation
model |
| Any cancer         |   |        |                   |                      |                                                          |                    |
| Unexposed          |   |        |                   |                      |                                                          |                    |
| Exposed – moderate |   |        |                   |                      |                                                          |                    |
| Exposed – severe   |   |        |                   |                      |                                                          |                    |
| Lung cancer        |   |        |                   |                      |                                                          |                    |
| Unexposed          |   |        |                   |                      |                                                          |                    |
| Exposed – moderate |   |        |                   |                      |                                                          |                    |
| Exposed – severe   |   |        |                   |                      |                                                          |                    |
| Breast cancer      |   |        |                   |                      |                                                          |                    |
| Unexposed          |   |        |                   |                      |                                                          |                    |
| Exposed – moderate |   |        |                   |                      |                                                          |                    |

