**Table 4. Number of events, accumulated person-time, and HRs for cancer associated with eczema activity, Denmark**

|            | N | events | P-Y
at
risk | Rate
per
1,000 | Hazard ratio and 99%
confidence interval  |                    |
|------------|---|--------|-------------------|----------------------|----------------------------------------------------------|--------------------|
|            |   |        |                   |                      | Unadjusted                                               | Mediation
model |
| Any cancer |   |        |                   |                      |                                                          |                    |

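### Severity and activity (item 6, Tables 3 and 4): the aim asks whether the association differs between eczema levels, but no between-level contrast, heterogeneity test or trend test is specified or reported

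*Protocol*

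**What the plan says.** The secondary aim (Objectives, Specific Aims and Rationale) is "To examine if the risk depends on severity and activity of eczema, age, sex, coexisting asthma and systemic immunosuppressive treatments". Item 6 under Subgroup analyses turns the first two of these into an analysis: "We will explore whether the association between eczema and cancer differs by eczema severity or eczema disease activity by stratifying separately on disease severity", and on activity in the same way.

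The exposure variables are defined under Exposure subgroups. For severity, "Severity will be included as a time-updated variable", with two exclusive states, moderate and severe. Activity is fixed over the first 12 months and has four codes, beginning "0=unexposed; 1=those who never had active atopic eczema in the first year", followed by active for less than 50% and for at least 50% of that year.

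The output is fixed by two table shells, "Number of events, accumulated person-time, and HRs for cancer associated with eczema severity, Denmark" (Table 3) and "Number of events, accumulated person-time, and HRs for cancer associated with eczema activity, Denmark" (Table 4). For each of 13 outcomes they have a row for unexposed and one for each eczema level, and two HR columns (unadjusted and mediation model) with 99% CIs. The footnotes repeat the main model: Cox regression on time since index date, stratified by matched set. No row, column or footnote compares one eczema level with another. The reference group is not named. Unexposed is implied by row order, by code 0, and by item 3, which compares eczema patients with the comparison cohort.

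**The concern.** Whether an association differs by level is answered by the difference between levels with its uncertainty. Two HRs that share a reference do not display that uncertainty. A reader left with the two printed intervals has two tempting shortcuts. One is to ask whether the intervals overlap, which is much stricter than a 99% comparison and can hide a real gradient. The other is to ask which interval excludes 1, which can suggest a gradient where there is none, because the smaller level has the wider interval. At stake is the conclusion on two named parts of the secondary aim.

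**Working it through.** The plan states no power, effect size or event count for these analyses, so there is no figure of its own to reproduce. Its only fixed numerical input here is the 99% level: z = 2.576.

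**1. Is the contrast identifiable?** Each matched set holds one eczema patient and up to 10 comparators (Unexposed cohort), and comparators are censored if they develop eczema (Follow-up). At any event time that patient is at exactly one level. Each term of the unadjusted stratified partial likelihood therefore involves only one level's coefficient, the information matrix is diagonal, and the level log-HRs are uncorrelated. So

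- contrast = log HR(severe) − log HR(moderate)
- SE = √(SE₁² + SE₂²)

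A simulation with assumed values (4,000 sets at 1:10, time-updated severity, true HRs 1.1 and 1.4, one binary covariate, 10,155 events) bears this out:

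| Model | Moderate HR | Severe HR | Correlation | Severe/moderate (99% CI) |
|---|---|---|---|---|
| Unadjusted | 1.15 | 1.57 | 0 | 1.36 (1.13 to 1.65) |
| Adjusted | 1.11 | 1.52 | 0.002 | 1.37 (1.132 to 1.666) |

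For the unadjusted row the variances are 0.00156 and 0.00403, so SE = √0.00559 = 0.0748 and the CI is exp(0.310 ± 2.576 × 0.0748). Ignoring the covariance changes nothing in the unadjusted model and gives 1.132 to 1.667 in the adjusted one.

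**2. Overlap reading.** Let r be the ratio of the two SEs. Two 99% CIs separate only when the difference exceeds 2.576 × (1 + r)/√(1 + r²) standard errors of the contrast.

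| r | Threshold (SE) | Effective two-sided alpha |
|---|---|---|
| 1 | 3.64 | 0.00027 |
| 2 | 3.46 | 0.00055 |
| 3 | 3.26 | 0.0011 |

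A direct 99% contrast needs 2.576 SE. Where it has 80% power the true difference is 2.576 + 0.842 = 3.417 SE. The overlap reading then has power P(Z > 3.643 − 3.417) = 0.41 at r = 1 and P(Z > 3.456 − 3.417) = 0.48 at r = 2.

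**3. Reading based on which CI excludes 1, with equal true HRs.** If p₁ and p₂ are the chances that each level's CI excludes 1 on the side of the true HR, exactly one does so with probability p₁(1 − p₂) + p₂(1 − p₁). With the larger level at 80% power:

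- r = 1: 2 × 0.8 × 0.2 = 0.32
- r = 1.5: p₂ = P(Z > 2.576 − 3.417/1.5) = 0.38, giving 0.57
- r = 2: p₂ = P(Z > 2.576 − 3.417/2) = 0.19, giving 0.68

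Using assumed eczema event counts instead, with variance 1/E + HR/(10E) for a level with E eczema events and 10 comparators per patient:

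| Common HR | 1,000 moderate, 100 severe | 1,000 moderate, 300 severe |
|---|---|---|
| 1.1 | 0.60 | 0.58 |
| 1.2 | 0.80 | 0.34 |
| 1.3 | 0.54 | 0.04 |

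**4. The lowest activity level.** A hospital record for eczema opens three active months, and the index date is itself the earliest such record. If it counts, every patient has at least 3/12 = 25% active time and the never-active level is empty. The text does not say whether it counts, and any comparison across levels depends on the answer.

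**The case against.** The strongest reply is that nothing is lost. The planned model contains the contrast, its point estimate is the ratio of two printed HRs, and in the unadjusted model its CI can be rebuilt exactly from the printed CIs. This stands. A reader might infer from the tables that the between-level comparison is never estimated or cannot be recovered; step 1 shows otherwise. The omission is one of specification and reporting.

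Second, the plan nowhere tells anyone to judge by CI overlap or by which interval excludes 1. It offers estimates, calls the work exploratory and makes it depend on power. This also stands: a reader might infer that judging by eye is the plan's rule, but no passage says so. Steps 2 and 3 measure the cost of shortcuts that the plan leaves open. Exploring whether an association differs still calls for an estimate of the difference, at least for overall cancer.

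Third, contrast statements are often left to a separate statistical analysis plan. That carries less weight here, since this document already fixes the model, the confidence level, the table shells and the footnotes. For melanoma stage (item 17) it even says how a pattern of HRs would be read; item 6 has no counterpart.

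Fourth, level-specific HRs against a common reference are a recognised description. They are, and they should stay. With one eczema patient per set, levels are never compared directly within a set, so the natural contrast is a ratio of two eczema-versus-comparator HRs, which is what item 6's wording asks for.

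**Conclusion.** The point holds as a gap between the question and the specified output: the aim and item 6 ask whether the association differs by severity and activity, and the plan neither specifies nor reports a between-level ratio, heterogeneity test or trend test. That unexposed is the reference is inferred, though soundly.

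The absence of correlation in the unadjusted model follows from the design. The near-zero correlation after adjustment rests on one simulation with a single covariate, so the model's own covariance should be used there. The overlap alphas depend on assumed SE ratios. The chance of a spurious one-level pattern runs from 0.04 to 0.80 across the assumed event counts, so no single figure describes this study.

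A reader might also take the rule against publishing results with fewer than 20 events as protection against sparse contrasts. It applies to outcomes as a whole, not to a thin severity or activity level within an outcome.

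**What to change.** In item 6 and in Tables 3 and 4, from the models already fitted:

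- Severity: add the severe/moderate ratio of HRs with its 99% CI, for both models.
- Activity: add the between-level ratios with 99% CIs, and one heterogeneity or trend test across all three eczema activity levels. First state whether the index hospital record counts as activity.
- State that conclusions about dependence on severity or activity rest on these contrasts, mainly for overall cancer, and that cancer-specific contrasts are exploratory. The restriction matters: one severity and one activity contrast for 13 outcomes in two models is already 2 × 13 × 2 = 52 comparisons.
- Name unexposed as the reference in both tables, and correct item 6's cross-references: it cites Tables 4 and 5, but severity and activity are Tables 3 and 4, and Table 5 is age.

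The cost is a linear contrast in the existing code, a few extra table rows and a few sentences of text; no new data are needed. The contrasts will be imprecise where a level has few events, and the tables should show that imprecision.
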